# The effect of a cognitive training therapy based on stimulation of brain oscillations in patients with mild cognitive impairment in a Chilean sample: study protocol for a phase IIb, 2 × 3 mixed factorial, double-blind randomised controlled trial

**DOI:** 10.1186/s13063-024-07972-7

**Published:** 2024-02-23

**Keywords:** Mild cognitive impairment, Cognitive training, Working memory, Cognitive functions, Non-invasive brain stimulation, Randomised controlled trial

## Abstract

**Background:**

The ageing population has increased the prevalence of disabling and high-cost diseases, such as dementia and mild cognitive impairment (MCI). The latter can be considered a prodromal phase of some dementias and a critical stage for interventions to postpone the impairment of functionality. Working memory (WM) is a pivotal cognitive function, representing the fundamental element of executive functions. This project proposes an intervention protocol to enhance WM in these users, combining cognitive training with transcranial electrical stimulation of alternating current (tACS). This technique has been suggested to enhance the neuronal plasticity needed for cognitive processes involving oscillatory patterns. WM stands to benefit significantly from this approach, given its well-defined electrophysiological oscillations. Therefore, tACS could potentially boost WM in patients with neurodegenerative diseases.

**Methods:**

This study is a phase IIb randomised, double-blind clinical trial with a 3-month follow-up period. The study participants will be 62 participants diagnosed with MCI, aged over 60, from Valparaíso, Chile. Participants will receive an intervention combining twelve cognitive training sessions with tACS. Participants will receive either tACS or placebo stimulation in eight out of twelve training sessions. Sessions will occur twice weekly over 6 weeks. The primary outcomes will be electroencephalographic measurements through the prefrontal theta oscillatory activity, while the secondary effects will be cognitive assessments of WM. The participants will be evaluated before, immediately after, and 3 months after the end of the intervention.

**Discussion:**

The outcomes of this trial will add empirical evidence about the benefits and feasibility of an intervention that combines cognitive training with non-invasive brain stimulation. The objective is to contribute tools for optimal cognitive treatment in patients with MCI. To enhance WM capacity, postpone the impairment of functionality, and obtain a better quality of life.

**Trial registration:**

ClinicalTrials.gov NCT05291208. Registered on 28 February 2022. ISRCTN87597719 retrospectively registered on 15 September 2023.

**Supplementary Information:**

The online version contains supplementary material available at 10.1186/s13063-024-07972-7.

## Administrative information

Note: the numbers in curly brackets in this protocol refer to the SPIRIT checklist item numbers. The order of the items has been modified to group similar items (see http://www.equator-network.org/reporting-guidelines/spirit-2013-statement-defining-standard-protocol-items-for-clinical-trials/).

## Introduction

### Background and rationale {6a}

Globally, sociodemographic changes reflect progressive population ageing. By 2050, the World Health Organization (WHO) projects that more than one in five people will be over 60, with 80% residing in low- and middle-income countries [1, 2]. This shift has increased the prevalence of chronic diseases, notably dementia, affecting cognitive, psychological, and behavioral functions, thereby challenging individuals, families, and public policies [3–5].

Conventional drug treatments for dementia have shown limited long-term efficacy, prompting the suggestion of non-pharmacological therapies as complementary treatments, particularly in the early stages like mild cognitive impairment (MCI) [6–8]. Working memory (WM), a vital cognitive component, has been identified as a modifiable factor through training, with evidence suggesting improved capacity and brain activity [9–11]

In neurodegenerative diseases, limited neuroplasticity poses challenges, but non-invasive brain stimulation (NIBS) could offer a promising avenue for enhancing cognitive rehabilitation. Integrating these advances into early intervention and cognitive training programmes for MCI patients remains an unexplored area.

#### Mild cognitive impairment (MCI)

MCI is clinically diagnosed based on observed cognitive changes, altered cognitive domains, independent daily living, and preserved functional and social performance [12]. This condition is considered a precursor to dementia, with specific profiles predicting the likelihood of different types of dementia. Amnestic MCI indicates a higher risk of developing Alzheimer’s disease, while a disjunctive predominance suggests frontotemporal dementia [13].

#### MCI and cognitive intervention

Studies have indicated the potential preservation of cognitive abilities and the partial reversibility of impairments in patients with MCI [14]. Environmental and lifestyle factors, including education, professional and leisure activities, and experiences, have been found to influence cognitive maintenance [15]. Considering the preventive role of cognitive training, it is reasonable to view it as a potential therapeutic tool. Improved performance has been observed in trained functions among subjects with single- and multiple-domain MCI [16]. Additionally, neurophysiological studies have shown alterations in brain oscillations in MCI patients similar to those seen in dementia patients [17].

#### MCI and non-invasive brain stimulation

Studies have demonstrated that altered brain oscillatory patterns underlie cognitive impairments in dementia [18, 19]. NIBS therapies can target these patterns, enhancing residual cognitive capacity at the early stage of impairment. Transcranial electrical stimulation, a validated and safe intervention, induces neuronal plasticity without directly triggering action potentials [20]. Among these techniques, transcranial direct current stimulation (tDCS) enhances excitability near the anode, while transcranial alternating current stimulation (tACS) modulates oscillatory activity to boost neuroplasticity [21]. Particularly, tACS offers a precise means of enhancing neuronal plasticity for cognitive processes like working memory (WM), given the detailed understanding of its underlying electrophysiological patterns [22].

#### Working memory (WM) and NIBS

Working memory (WM) is a crucial cognitive capacity facilitating the temporary manipulation of information for future behavioral guidance. Its neural basis involves distributed functional networks primarily in fronto-parietal association cortices, with theta and nested gamma oscillations [23–26]. Alterations in brain oscillatory dynamics, especially in the theta and gamma frequency ranges, have been linked to cognitive impairments in various neurodegenerative diseases, indicative of potential early cognitive reserve loss [18, 19, 27–29].

Implementing WM training programmes has demonstrated improved cognitive performance, attributed to increased activity, connectivity, and selectivity within fronto-parietal networks, potentially explaining the observed transfer effect to enhance daily functionality [11].

#### Cognitive training and NIBS in MCI Patients

To date, no initiatives offering interventions combining cognitive training and neuroplasticity facilitation have been made available for individuals with MCI. Studies have shown the medium-term efficacy of tDCS in enhancing working memory (WM) in the older adult population [30]. However, evidence suggests that tACS may be more efficient than tDCS in improving WM [22]. Clinical trials in progress are investigating the combined impact of tDCS and WM training in MCI [31, 32].

Given the need for effective therapeutic alternatives to enhance the quality of life and reduce cognitive disability, this study proposed to evaluate the effect of a WM training therapy, which involves tACS on the prefrontal oscillatory activity, in a group of users with MCI compared to an intervention involving only cognitive training. Recent research demonstrates the potential of oscillatory electrical stimulation, particularly a specific gamma wave (80 Hz) synchronised with the positive phase of theta oscillation (6 Hz), in enhancing WM and increasing connectivity within brain regions [33]. This evidence supports the notion that brain oscillatory activity can be targeted for cognitive training, fostering neuroplasticity [34].

### Objectives {7}

#### Aims

To evaluate the effect of a combined cognitive training programme (CCTP) that involving cognitive training and transcranial alternating current electrical stimulation on prefrontal oscillatory activity in a group of patients with mild cognitive impairment, compared to a traditional cognitive training programme (TCTP) involving only cognitive training.

##### ***Hypothesis***

We hypothesise that:

MCI patients who participate in the combined cognitive training programme (CCTP) present a pre-post-intervention increase in prefrontal theta oscillatory activity, which will be greater than the increase submitted by those patients who participate in the traditional cognitive training programme (TCTP).The increase in prefrontal theta oscillatory activity generated by the combined cognitive training program (CCTP) is reflected in an addition in the cognitive performance post-intervention of patients with MCI concerning their cognitive performance pre-intervention.

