### Outcomes {12}

#### Primary outcome

The primary result will be prefrontal theta oscillatory activity. This continuous variable is sensitive to electrophysiological changes underlying cognitive processes as WM. It has been described in several works of our group and others [28, 38–43]. The primary timepoint for outcome measures will be three times: pre-intervention, 1 and 12 weeks post-intervention. This outcome corresponds to the ratio of the normalised power (mean/standard error, mV^2^) of the prefrontal theta oscillation (5–10 Hz, F3 electrode) related to successful memory performance (SMP). This prefrontal theta oscillation is calculated based on a single-trial general linear model that includes SMP as the regressor of interest and memory load as a secondary regressor.

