### Sample size {14}

For the estimation of the minimum required sample size, we will consider the following parameters: (a) Effect size for the mixed ANOVA statistical test (2 × 2, with interaction effects), (b) Statistical power (1 − *β*) = 0.95 and (c) Significance level α = 0.05. We will use the G*Power 3 software to calculate [47]. Considering an effect size *η*^2^ = 0.06, the sample size amounts to 54 participants (n1 = 27; n2 = 27). As our study will be a two-intervention effect, we will consider an effect size somewhat smaller than those observed for comparisons between clinical populations of prefrontal theta oscillations during working memory: for example, Lenartowicz: *η*^2^ = 0.09 [38], and which coincides with the work of our team *η*^2^ ~ 0.1 [28]. The effect size we will use to calculate the sample is considered a moderate to significant effect according to Cohen’s criteria [48]. However, the initial sample size we propose in this project finds the proportion of participants who may present low adherence to the study. In this regard, we can point out that in a preliminary study with similar characteristics, a drop-out rate of about 15% was observed. Therefore, considering the drop-out percentage and the minimum sample size required to investigate an effect, the initial sample will be 62 participants (n1 = 31; n2 = 31).

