#### Inferential analysis

Compliance with assumptions for parametric testing will be contrasted. In particular, univariate normality (i.e. Kolmogorov-Smirnoff, Shapiro–Wilk), sphericity (i.e. Mauchly’s W), and homoscedasticity of error variances (i.e. Levene test). If any of the above assumptions are violated, the corresponding non-parametric estimates will be provided. Mixed-model analyses without any ad hoc imputations will be used to handle missing data in case of participant drop-out and to conduct the efficacy analysis [53]. To assess distributional assumptions and the impact of missing random effect components on the model, several tests will be conducted. Normality assumptions will be examined using the Shapiro–Wilk test, skewness and kurtosis indices, and normality plots (Q-Q plots). Homoscedasticity will be investigated using Levene’s test and Box’s M test for equivalence of covariance matrices. The Wald statistic (or *Z*-test) will be utilised to test residual error variance estimation and the null hypothesis of homogeneity of residuals. The assumption that data is missing completely at random (MCAR) will be assessed using Little’s MCAR test, which remains robust to violations of distributional assumptions [54]. Additionally, the primary outcome will be evaluated using Bayesian hierarchical approaches employing JAGS and R software. In this approach, each individual beta per regressor will be subjected to a population distribution of beta values that follow a normal distribution [55]. The prior assumption for each population distribution of beta values will be flat (non-informative). The correct convergence of the Markov Chain Monte Carlo (MCMC) will be evaluated using the Gelman-Rubin statistic. The model fit will also be assessed using DIC (Deviance Information Criterion) and LOOIC (Leave-One-Out Information Criterion).

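### The aim and hypothesis 1 speak of a rise in prefrontal theta, but the primary outcome, on its most natural reading, is a success-related effect over its standard error and cannot by itself show such a rise

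*Protocol article*

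**What the plan says.** The Aims section of the protocol article sets out to evaluate training combined with "transcranial alternating current electrical stimulation on prefrontal oscillatory activity in a group of patients with mild cognitive impairment". Hypothesis 1 predicts that patients in the combined programme (CCTP) will "present a pre-post-intervention increase in prefrontal theta oscillatory activity, which will be greater than the increase submitted by those patients" in the traditional programme (TCTP). Neither statement mentions trial success.

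The Primary outcome section uses the same label: "The primary result will be prefrontal theta oscillatory activity". It then narrows the meaning: "This outcome corresponds to the ratio of the normalised power (mean/standard error, mV^2^) of the prefrontal theta oscillation (5–10 Hz, F3 electrode", related to SMP. The quantity is "calculated based on a single-trial general linear model that includes SMP as the regressor of interest and memory load as a secondary regressor".

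Two other places bear on how to read this:

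- Secondary outcomes, item 3, defines parietal theta at CP3 from a model with the same two regressors but exchanges their roles, so that memory load is the regressor of interest.
- Inferential analysis adds a Bayesian model of the primary outcome in which "each individual beta per regressor will be subjected to a population distribution of beta values that follow a normal distribution".

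Overall theta power is not listed among the primary or secondary outcomes.

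**The concern.** The aim and hypothesis 1 are worded as a question about level: does prefrontal theta increase, and does it increase more in CCTP? The outcome definition appears to answer a question about a contrast: how far does theta differ between successful and failed trials at equal memory load, relative to the precision of that estimate? In a model of this kind the overall level sits in the intercept, which the outcome does not use.

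What is at stake is the conclusion. A null primary result could be reported as no effect on prefrontal theta when theta had risen on all trials. A positive result could be reported as an increase in theta when the only change was less theta on failed trials. Because the hypothesis and the outcome share one label, a reader of the results would have no warning of either.

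**Working it through.** **1. What the outcome is.** The article never writes the phrase coefficient over standard error, so this is inferred. Three features support it: a regressor of interest is named; the parietal outcome differs by exchanging the regressor roles, which would make no difference if the outcome were mean power; and the Bayesian analysis works on one beta per regressor. The printed unit, mV², does not fit a ratio of mean to standard error, so some ambiguity remains.

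**2. Algebra.** For one participant and visit, let y be single-trial theta power, S success (0/1) and L load:

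y = β0 + β1·S + β2·L + e, with ratio R = b1 / SE(b1).

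Replace y by a + c·y on every trial, with c > 0. Then b1 becomes c·b1, every residual is multiplied by c, and SE(b1) becomes c·SE(b1). R is unchanged. Only the intercept takes up a, becoming a + c·b0.

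**3. Illustration.** Assumed values, not from the article: 200 trials, success probability 0.7, loads 2, 4 and 6, y = 10 + 1.0·S + 0.3·L + noise with SD 3.

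| Change in theta | Mean power | b1 | SE | R |
|---|---|---|---|---|
| none | 12.12 | 0.470 | 0.411 | 1.144 |
| +5 on every trial | 17.12 | 0.470 | 0.411 | 1.144 |
| ×1.5 on every trial | 18.17 | 0.704 | 0.616 | 1.144 |
| +1 on successful trials only | 12.81 | 1.470 | 0.411 | 3.579 |
| −1 on failed trials only | 11.81 | 1.470 | 0.411 | 3.579 |

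The last row follows from the one above it. Taking 1 from failed trials equals adding 1 to successful trials and then taking 1 from all, so R is the same and mean power is 12.81 − 1 = 11.81. R triples while theta falls.

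**4. Trial level.** Simulation with 27 per arm, 120 trials per visit and 500 runs, under assumed between-person and between-visit variation. The pre-post change was compared between arms at 0.05.

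| Change in CCTP only | Significant with R | Significant with mean power |
|---|---|---|
| +2 on every trial | 4.6% | 99.8% |
| ×1.2 on every trial | 6.4% | 100% |

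The simulation error around a true 5% is √(0.05 × 0.95 / 500) ≈ 1 percentage point, so both figures in the R column are compatible with the nominal error rate.

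**5. The other reading.** If mean/standard error is taken over the power of successful trials, it moves from 53.25 to 74.93 with +5 on every trial but stays at 53.25 with ×1.5. A proportional rise remains invisible; an additive one does not.

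**6. Sample size.** The article asks for "Statistical power (1 − *β*) = 0.95 and (c) Significance level α = 0.05" with η² = 0.06. Then f² = 0.06/0.94 = 0.0638. With two measurements and a correlation of 0.5 (not stated in the article; assumed as the software default), λ = 0.0638 × 54 × 2 / 0.5 ≈ 13.8 on 1 and 52 degrees of freedom, which gives power 0.954. The stated 54 is reproduced. Nothing in this point alters it.

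**The case against.** The strongest reply is that the Primary outcome section is the working definition of the term used in hypothesis 1. Stating a construct in the hypothesis and defining it under outcomes is normal. The article's wider language supports this: the rationale is plasticity for working memory, stimulation is given during a verbal working memory task, and the EEG outcomes after treatment are taken at 1 and 12 weeks, when no stimulation is planned. On that reading hypothesis 1 already concerns success-related theta and cannot be true while the endpoint is unchanged. This stands as a possible reading. It does not remove the need to say so, because neither the aim nor hypothesis 1 carries the restriction and a reader of the results would take the broader sense.

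Other replies also stand in part:

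- Coefficient over standard error is inferred, and on the alternative reading an additive rise would register.
- The invariance needs the same shift or gain on every trial, with no added trial noise. Nothing in the article says that stimulation acts this way, and a rise confined to successful trials would be detected.
- The Bayesian analysis uses betas. If power enters that model unscaled, a proportional gain would move a non-zero beta (0.470 to 0.704 above), though an additive shift would not.
- A theta level expressed only relative to a pre-trial baseline could itself cancel a general gain, so the added estimate needs care.

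A reader might infer that hypothesis 1 could be true and yet be rejected. The article does not support that. It requires reading the hypothesis as overall theta power, and a null result would only leave the hypothesis unsupported.

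**Conclusion.** The point holds as a cheap improvement. The aim and hypothesis 1 are worded as an increase in theta activity. The primary outcome, on its most natural reading, is a success-related effect scaled by its standard error. That ratio does not respond to a uniform additive or proportional rise, and it can rise with no increase in theta, so it does not by itself show whether theta activity increased.

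The invariance is exact under two assumptions: that the outcome is the SMP coefficient over its standard error, and that the change is identical on every trial. Where both hold, a uniform rise is detected at about the significance level only. The illustrative values depend on assumed trial numbers and variances; the invariance does not.

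It would go too far to conclude that the endpoint is the wrong choice or that the sample size must change. A success-related contrast is a legitimate primary outcome, and its parallel use for parietal theta suggests that it is deliberate. What needs aligning is the wording of the claim.

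**What to change.** 1. Restate the aim and hypothesis 1 as an increase in success-related (SMP) prefrontal theta modulation, greater in CCTP than in TCTP. Limit the primary conclusion to that. Keep the present endpoint as primary.
2. Add, labelled as secondary, the F3 theta level during the task: the prediction from the same single-trial model at mean load and mean SMP. Give it in absolute or log power, not only relative to a pre-trial baseline.
3. Report this level by arm and visit beside the SMP coefficient, so that a general rise, a selective rise and a fall on failed trials can be told apart.

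The change is to wording, plus one extra reported EEG estimate from recordings and a model that the trial already needs. It should be settled before unblinded results are seen. No new data collection and no change to the sample size are required.

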### Trial design {8}

This study is a phase IIb randomised, double-blind clinical trial type study. It will be a parallel design where two groups receive two treatments (interventions). We will study the characteristics of the factors and effects. In this manner, this analysis will allow us to conceptualise the design as a 2 × 3 mixed factorial. Thus, we will include a factor between groups (type of intervention, two levels) and an intra-subject factor (measured in three episodes, one pre-intervention, and two post-intervention). Based on the factor between groups, it will implement two different interventions. The treatment group will receive a cognitive training intervention combined with alternating current electrical stimulation (i.e. treatment). The control group will receive a traditional cognitive training intervention with placebo electrical stimulation. Depending on the intra-subject factor, two dependent variable measurements will be implemented: one pre-intervention and one post-intervention measure. This design will allow the study of the potential interaction effects between the inter- and intra-subject factors [35].

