### Intervention description {11a}

In the CCTP, the patients will be organised into groups composed of three participants. The patients will realise a combined electrical stimulation and cognitive training programme. That contemplates 12 WM training sessions based on tasks of storage and manipulation of verbal and visuospatial information, with a frequency of twice a week for 6 weeks, completing a total of 12 sessions in presential format. Concomitantly, the participants will receive real electrical stimulation for 10 min during a verbal working memory task. The intervention will be delivered by trained personnel in this technique and an assistant to groups. This electrical stimulation protocol includes 10-s periods of phase-in and 10 s of phase-out and will be done in parallel with the cognitive intervention programme in sessions 3, 4, 5, 6, 7, 8, 9, and 11. The electrical stimulation will be applied with two 3 × 1 arrays of electrodes. The central stimulation electrodes will be positioned in F3 and CP3 (according to the international 10–20 system). The AC stimulation will be one mA from the baseline to the stimulation peak. The stimulation will have a gamma sine waveform (80 Hz) over the positive phase of the theta oscillation[33] individualised for each patient ranging from 4 to 8 Hz and the phase-locked between arrays [36, 37]. The electrode impedances will always be maintained under 10 kOhms.

Participants in the control group (TCTP) will start a cognitive intervention programme identical to the treatment group and will be organised into groups of three participants. Still, unlike the treatment group, they will receive placebo electrical stimulation, i.e. an electrical current will be applied for a short period at the beginning of the session (30 s). Then, the electric stimulation will be stopped. This procedure induces a sensation in the skin similar to real electric stimulation without generating a detectable impact on the brain state. They will be performed parallel to the cognitive intervention programme in sessions 3, 4, 5, 6, 7, 8, 9, and 11.

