#### Secondary outcomes

Secondary results will correspond to performance measures in validated test work memory tasks:

The secondary timepoint for outcome measures will be three times: pre-intervention, 1 and 12 weeks post-intervention.

(1) WAIS-IV Digit Retention subtest. Chilean standard [44]

It is part of the WM Index and consists of three tasks: (a) Direct Digits: repeat a series of digits, presented orally, in the same order as they are presented; (b) Reverse Order Digits: repeat a series of digits in reverse order as they are presented; and (c) Sequence Digits: order and repeat from lowest to highest a series of numbers read by the examiner. These tasks assess attention and resistance to distraction, immediate auditory memory, and WM.

(2) Trail Making Test B (TMT-B). Chilean standard [45]

This part of TMT reflects mainly WM and, secondarily, the capacity for cognitive flexibility [46]. It connects 25 numbers and letters in ascending order, alternating between them (e.g. 1-A, 2-B, 3-C, etc.). The score is obtained when it takes an individual to complete the task.

(3) Parietal theta oscillatory activity. The ratio of the normalised power (mean/standard error, mV^2^) of parietal theta oscillation (5–10 Hz, CP3 electrode) related to memory load. This parietal theta oscillation is calculated based on a single-trial general linear model that includes memory load as the regressor of interest and successful memory performance (SMP) as a secondary regressor.

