The effect sizes will be reported for each electrophysiological and cognitive performance measure analysis through the index η^2^p (partial eta square). The respective post hoc comparisons will use Bonferroni’s correction, and the effect size will be reported through Cohen’s index *d*. Graphs of the interaction effects will be provided if observed. In case of transgression of the sphericity assumption, the Greenhouse–Geisser correction will be made. Consequently, the respective parametric statistics will be provided (i.e. Friedman test, Connover’s post hoc tests). For all hypothesis tests, a significance level will be considered *⍺* = 0.05.

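### Hypothesis 2 states the cognitive benefit as a post- versus pre-intervention gain with no TCTP comparator, so shared training and retest gains could meet it without any stimulation effect

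*Protocol article*

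**What the plan says.** The Hypothesis section of the protocol article makes two statements, unnumbered there and called Hypothesis 1 and Hypothesis 2 here.

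- Hypothesis 1 concerns prefrontal theta and is comparative. It expects a pre-to-post increase in CCTP "which will be greater than the increase submitted by those patients who participate in the traditional cognitive training programme (TCTP").
- Hypothesis 2 concerns cognition. The theta increase produced by CCTP "is reflected in an addition in the cognitive performance post-intervention of patients with MCI concerning their cognitive performance pre-intervention". TCTP is not mentioned.

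Four other places bear on how Hypothesis 2 can be read.

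- **Shared training.** Under Intervention description {11a}, TCTP participants "will start a cognitive intervention programme identical to the treatment group", with placebo in place of real stimulation.
- **Gains from training alone.** The section on MCI and cognitive intervention states: "Improved performance has been observed in trained functions among subjects with single- and multiple-domain MCI". The section on working memory and NIBS adds: "Implementing WM training programmes has demonstrated improved cognitive performance".
- **Repeated tests.** Under Secondary outcomes: "The secondary timepoint for outcome measures will be three times: pre-intervention, 1 and 12 weeks post-intervention". The cognitive measures are WAIS-IV Digit Retention and TMT-B.
- **Design and analysis.** Trial design {8} says of the mixed factorial layout: "This design will allow the study of the potential interaction effects between the inter- and intra-subject factors". The Inferential analysis section plans mixed models for efficacy, effect sizes for each electrophysiological and cognitive measure, graphs of any interaction, and a multiplicity correction: "The respective post hoc comparisons will use Bonferroni".

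**The concern.** A post- versus pre-intervention gain in CCTP combines three things: the training, familiarity with tests taken before, and any effect of stimulation. Only the last separates the arms. The article's own rationale predicts the first, and repeated testing makes the second plausible. A gain in CCTP is thus to be expected even if stimulation does nothing.

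Tying the gain to the theta increase does not isolate stimulation either. That increase is attributed to the whole combined programme, which includes the training.

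At stake is what the trial may say about its cognitive outcomes, which are the ones closest to patient benefit. A report could describe the cognitive hypothesis as supported when CCTP and TCTP had improved equally, and it would be faithful to the hypothesis as written.

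**Working it through.** **1. The contrasts side by side**

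| | Outcome | Contrast stated | TCTP named? |
|---|---|---|---|
| Hypothesis 1 | Prefrontal theta | Increase in CCTP against increase in TCTP | Yes |
| Hypothesis 2 | Cognitive performance | Post- against pre-intervention | No |

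The Aims paragraph is comparative but names only prefrontal oscillatory activity, so it does not supply the missing comparator. No other section restates Hypothesis 2 as a between-arm contrast. If its reference to patients with MCI is read as covering both arms, the contrast is still post against pre, without a control.

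**2. The plan's own figure**

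Sample size {14} gives 54 participants (27 per arm) for a 2 × 2 mixed ANOVA with interaction, η² = 0.06, power 0.95 and α = 0.05.

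- f² = 0.06 / 0.94 = 0.0638, so f = 0.2526.
- λ = f² × N × m / (1 − ρ), with m = 2 measurements and ρ = 0.5. The value of ρ is the G*Power default and is an assumption here, since the article does not state it.
- N = 54: λ = 0.0638 × 54 × 2 / 0.5 = 13.79. On 1 and 52 degrees of freedom the power is 0.954.
- N = 52: the power is 0.947, below the target.

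So 54 reproduces, and it is sized on the interaction, not on a within-arm change.

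**3. How easily a within-arm gain appears when stimulation adds nothing**

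Inputs:
- n = 27 CCTP completers, from Sample size {14}.
- True stimulation effect of zero.
- A gain shared by both arms of d_z = 0.2 to 0.5 SD of change. The article gives no such gain, so this range is an assumption.

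Formula: the probability of significant improvement in a two-sided paired t-test is P(T > t_crit), where T is noncentral t with 26 degrees of freedom and noncentrality d_z × √27 (√27 = 5.196).

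- α = 0.05: t_crit = 2.056.
- Bonferroni for the three pairwise comparisons among three visits (the number is an assumption): α = 0.05 / 3 = 0.0167, t_crit = 2.559.

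| Shared gain (SD of change) | Noncentrality | Uncorrected | Bonferroni, 3 comparisons |
|---|---|---|---|
| 0.2 | 1.04 | 17% | 8% |
| 0.3 | 1.56 | 32% | 18% |
| 0.4 | 2.08 | 52% | 33% |
| 0.5 | 2.60 | 71% | 52% |

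With no shared gain the uncorrected figure is 2.5%, because only improvement is counted.

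**4. The between-arm test under the same conditions**

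In 20,000 simulated trials per setting (27 per arm, zero stimulation effect, shared gains of 0 to 0.5 baseline SD, pre-post correlation 0.5 or 0.7), the two-sided test of the difference in change was significant in 4.6% to 5.1% of trials. The shared gain cancels, whatever its size.

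**5. What these percentages are not**

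Step 3 describes one paired test on one cognitive score. Hypothesis 2 also requires a theta increase that the cognitive gain reflects. That condition can only lower the chance of confirmation, so for one test at a given gain the percentages are an upper bound.

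**The case against.** The strongest reply is that the analysis already does the right thing. The design is a mixed factorial with a between-group factor, the sample size rests on the interaction, efficacy is assessed by mixed models, and effect sizes and interaction graphs cover the cognitive measures as well as theta. This stands. A reader might infer from Hypothesis 2 that the plan decides the cognitive question on a paired CCTP test, or that it gives up the randomised comparison for cognition. The article supports neither reading. No section names such a test as decisive, and the sentence on post hoc comparisons specifies no contrast.

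A second reply is that Hypothesis 2 builds on Hypothesis 1. If support for it first requires a larger theta increase in CCTP than in TCTP, that premise would hold only at the type I error rate when stimulation adds nothing to theta. The wording allows this reading but does not require it. The reply therefore limits the percentages to an illustration and leaves the missing comparator as it is.

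A third reply concerns the link between theta and cognition. One might fault the article for describing no analysis that relates the two changes. That is not a fair criticism here: a journal article may leave such a model to the statistical analysis plan, which is not shown.

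The analysis plan cannot be relied on to repair the hypothesis in the same way. The hypothesis is set in this document, and a plan that tested the between-arm contrast would be testing something other than what it says.

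**Conclusion.** The point holds as a fault of wording. Hypothesis 2 leaves out the comparator that Hypothesis 1 includes. With identical training and repeated tests in both arms, the stated contrast can be met without a stimulation effect.

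This conclusion needs only that some shared gain is plausible, which the article's rationale asserts. The ranges of 17% to 71% uncorrected and 8% to 52% with Bonferroni show the order of magnitude. They rest on the assumed gains, 27 completers and, for the second range, three comparisons, and they leave out the theta condition.

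The design, the planned model and the sample size for the primary outcome are unaffected. What changes is the cognitive claim that the trial may make.

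**What to change.** Reword Hypothesis 2 so that it predicts a greater pre-to-post improvement in Digit Retention and TMT-B in CCTP than in TCTP. State that it is judged by the group-by-time contrast of the mixed model already planned. Report changes within each arm descriptively, not as tests of the hypothesis. Secondary outcomes lists 1 and 12 weeks without ranking them, and this point does not require choosing between them.

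The change should be made before the allocation codes are broken. It costs wording only, with no new data and no change to the number randomised. The price is a claim that is harder to meet, because a shared gain no longer counts towards it.
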